### Data collection

#### Baseline data collection

All participants will give consent for access to their primary care records. These, alongside a brief questionnaire, will provide participant baseline data including demographics, medication and co-morbidities that cover the Charlson index^41^ (giving an overall score for co-morbidity) and other prevalent co-morbidities in the study population (table 1).^42^ Participants are not asked to complete further data collection activities during the 12-month follow-up period as we want to minimise the potential Hawthorne effect in our control group. We are concerned that prolonged exposure to the research team could lead usual care participants to change their behaviour and either seek or perhaps decline liver assessment.^43^

**Table 1 T1:** Baseline participant characteristics that will be collected and where the data will be collected

Baseline demographic characteristic	Collected at recruitment	Can be collected via EMIS/SystmOne*
Age, years	✓	
Sex, male (%)	✓	
Ethnicity (white European or minority ethnic group)	✓	
Alcohol consumption (AUDIT-C score)	✓	
Measured height (cm)		
Measured weight (kg)	✓	
Smoking status (current, ex, never)		✓
Index of multiple deprivation (from postcode)	✓	
Duration of diabetes (years)		✓
Medical treatment for diabetes—tablets or insulin (currently, previously, never)	✓	
**Currently prescribed medications**		
Antiglycaemic treatment (any)	✓	
Sulphonylurea (eg, gliclazide)	✓	
Metformin	✓	
Insulin	✓	
GLP-1 agonist (eg semaglutide)	✓	
Pioglitazone	✓	
SGLT2 inhibitor (eg flozins)	✓	
Anticoagulants (DOAC or warfarin)	✓	
Antihypertensives (any)	✓	
ACE (eg ramipril)	✓	
ARBs (eg candesartan)	✓	
B-blockers (eg bisoprolol)	✓	
Thiazides (eg BTZ)	✓	
Calcium channel blockers (eg amlodipine)	✓	
Antidepressants	✓	
Fibrates	✓	
Statins	✓	
**Co-morbidities (to calculate Charlson co-morbidity index)**		
Definitive or probable previous myocardial infarction	✓	✓
Congestive heart failure (dyspnoea with response to CHF medication)	✓	✓
Peripheral vascular disease (intermittent claudication, previous by-pass grafting)	✓	✓
Any end organ damage due to T2DM	✓	✓
Moderate to severe chronic kidney disease	✓	✓
Solid tumour (non-localised, metastatic)	✓	✓
Lymphoma (either cured, in remission or active)	✓	✓
Hemiplegia	✓	✓
AIDs	✓	✓
Peptic ulcer disease	✓	✓
Connective tissue disease (eg SLE, rheumatoid arthritis, not osteoarthritis)	✓	✓
**Additional prevalent comorbidities in patients with T2DM**	✓	✓
Hypertension	✓	✓
Asthma	✓	✓
Hypothyroidism	✓	✓

* EMIS and Systm1 are primary care software programmes used throughout England.

ACEangiotensin converting enzymeARBangiotensin receptor blockerAUDIT-CAlcohol Use Disorders Identification Test-ConsumptionBTZbendroflumethiazideCHFcongestive heart failureDOACDirect Oral AnticoagulantsGLP-1glucagon-Like peptide-1 receptor agonistSGLT2sodium/glucose cotransporter 2SLESystemic Lupus ErythematosusT2DMtype 2 diabetes mellitus

#### Primary outcome data collection

The primary outcome—referral to HCC surveillance following a referral with suspected liver disease from primary care will be assessed by the research team from each participant’s healthcare records. Participants will not need to be recontacted for outcome data. For standard care participants, the primary care record will be reviewed for a referral letter to secondary care or a community liver assessment service that was sent within 12 months of randomisation. For both trial arms, records will be reviewed for evidence (eg a letter from hepatology services) that the patient has been enrolled in HCC surveillance. The primary care record review will take place up to 30 months from randomisation to ensure enough time for definitive decisions regarding HCC surveillance to have been made by the clinical team.

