## Abstract

**Introduction:**

Hepatocellular carcinoma (HCC) is expected to become the third most common cause of cancer death worldwide by 2030. The increase in HCC is in large part due to the rising prevalence of risk factors such as type 2 diabetes mellitus (T2DM). Up to 1 in 20 people living with T2DM have liver cirrhosis, and they have a 1% to 2% incidence of HCC per year. Patients with cirrhosis enter surveillance for HCC to identify early-stage, curable tumours. A diagnosis of T2DM does not mandate testing to identify patients with cirrhosis, with testing restricted to those with additional risks. There has never been a trial and nested cost-effectiveness evaluation comparing screening all patients with T2DM for cirrhosis against usual care.

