**Methods and analysis:**

The study will use a multi-centre, unblinded individual randomised controlled trial design. The aim will be to determine the effectiveness and cost-effectiveness of screening all adults with T2DM to identify those at high risk of HCC. The recruitment strategy has been supported by patient and public involvement (PPI). Participants will be identified via an automated search of primary care records and invited to participate via text. 320 participants will be randomised for screening. The screening will include measurement of bio-markers for liver fibrosis (ELF and Fib-4) and vibration-controlled transient elastography. Another 320 participants will be randomised to standard care. Demographic and medical history data will be collected at baseline from all participants. Outcome data will be collected remotely from healthcare records. The primary outcome is the proportion of participants in each arm who are referred to HCC surveillance following testing for liver disease within 12 months of randomisation. The results will be used to calculate the incremental cost-effectiveness ratio of screening via a Markov model.

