### Primary outcome

The number of participants referred to secondary care with the suspected liver disease within 12 months of randomisation who are subsequently referred for HCC surveillance.

As an unblinded trial, it is important our primary outcome is as objective as possible and independent of the research team. In both study arms, patients with high liver stiffness measurements will be referred to nearby hepatology services (with thresholds defined by local practice). Via usual care, an independent local clinician will then assess the severity of liver disease. In real-world practice, this may include history, examination, no further tests or repeat VCTE, additional tests for fibrosis and in some cases liver biopsy. Regardless of the clinical approach taken, the primary outcome will be whether the clinician felt the disease was severe enough to warrant referral for HCC surveillance. Since the trial sites cover a variety of different regions across the south of England, this pragmatic approach is likely to closely reflect current UK practice.

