### Arm 1—screening

Participants in this arm will be referred by the research team directly for liver fibrosis assessment at a community hub. This assessment will include VCTE and venepuncture for an ELF test and a FIB-4 index. The result of the VCTE and any abnormalities identified in the blood tests will be managed by the local liver disease care pathway (as per the usual care arm described below). VCTE will be performed by an experienced single operator after a minimum of a 3-hour fast and previously published criteria for a valid reading will be applied to each participant.^40^

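### The primary outcome is defined in three different ways, and the 12-month referral-letter check is stated for controls only, so usual care's yield may be undercounted

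*Protocol article*

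**What the plan says.** The protocol article states the primary outcome in three places.

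- Abstract, Methods and analysis: the proportion "referred to HCC surveillance following testing for liver disease within 12 months of randomisation".
- Primary outcome, as its own section gives it: "The number of participants referred to secondary care with the suspected liver disease within 12 months of randomisation who are subsequently referred for HCC surveillance".
- Primary outcome data collection: "referral to HCC surveillance following a referral with suspected liver disease from primary care".

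The data-collection section then says how the outcome is to be found. One step is given for controls: "For standard care participants, the primary care record will be reviewed for a referral letter to secondary care or a community liver assessment service", with the letter sent within 12 months of randomisation. Another is given for everyone: "For both trial arms, records will be reviewed for evidence (eg a letter from hepatology services) that the patient has been enrolled in HCC surveillance".

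Arm 1 has its own section, which describes a different way into assessment: "Participants in this arm will be referred by the research team directly for liver fibrosis assessment at a community hub".

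The trial is unblinded, the research team assesses the outcome from records, and the analysis keeps all randomised participants in their assigned arm. The Data analysis section expects small outcome numbers.

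**The concern.** The three statements set different qualifying steps: a test, a referral to secondary care from an unnamed source, and a referral from primary care. They agree for the typical case, a patient whose GP refers after an abnormal test. They can disagree for a control whose disease comes to light elsewhere, for example on hospital imaging, during an admission, or through another specialist who refers directly to hepatology.

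The evidence rule is also uneven. A control must pass a dated letter check as well as show enrolment in surveillance. For the screening arm only the enrolment check is described, and the primary-care wording does not fit an arm that enters assessment through the research team.

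At stake is the control event count. The introduction gives ignorance of how standard care performs in practice as one reason for the trial. A rule that may leave out part of what standard care finds would lower the control proportion and push the odds ratio towards screening. In an unblinded trial, which definition applies should not be left to the person extracting the record.

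**Working it through.** **Step 1. Apply each wording to the same participants.** All are assumed to be referred to HCC surveillance in the end, with the first step inside 12 months.

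| Participant | Abstract | Primary outcome section | Data-collection section, read literally |
|---|---|---|---|
| Control, referred by GP | Event | Event | Event |
| Control, referred to hepatology by another hospital specialist after testing | Event | Event (no referrer named) | Non-event: not from primary care |
| Control, tested and diagnosed during an admission or after incidental imaging | Event | Unclear: depends on what counts as referral to secondary care | Non-event: not from primary care |
| Screened, found at the hub and sent on to hepatology | Event | Event | Unclear: entry was through the research team, and no letter check is stated |

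Rows 2 and 3 change status with the section applied. Row 4 shows that the primary-care wording does not describe the screening arm's route.

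**Step 2. Direction.** A loss of the kind in rows 2 and 3 can occur in either arm, because a screened participant who misses the hub visit could also be found in hospital. Most screened participants with advanced disease should already have been picked up at the hub, so the loss should fall mainly on controls. That favours screening.

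**Step 3. The plan's own figures.** The Sample size section gives 320 per arm, at least 80% power with 25% drop-out (320 × 0.75 = 240 per arm) and more than 90% with 5% drop-out (320 × 0.95 = 304 per arm). The event rates, alpha and sidedness are not in the text; the section points to figure 3, which is not shown. The power therefore cannot be reproduced. As a consistency check, assumed rates of 4% v 0.25% at two-sided 0.05 give exact Fisher power of 80.5% at 240 per arm and 91.5% at 304, in line with the stated figures. Nothing here shows the stated power to be wrong.

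**Step 4. Sensitivity to one lost control event.** The counts are assumed, at 320 per arm. Crude odds ratio = [a/(320 − a)] ÷ [c/(320 − c)], with a screening events and c control events counted. The adjusted version adds 0.5 to each cell, a simple stand-in for the planned penalised estimate. For 10 v 3 the crude value is (10 × 317)/(3 × 310) = 3.41; for 10 v 2 it is (10 × 318)/(2 × 310) = 5.13.

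| Screening v control | Risk difference (points) | Crude OR | OR with 0.5 added | Two-sided Fisher p |
|---|---|---|---|---|
| 10 v 3 | 2.19 | 3.41 | 3.07 | 0.089 |
| 10 v 2 | 2.50 | 5.13 | 4.31 | 0.037 |
| 12 v 3 | 2.81 | 4.12 | 3.68 | 0.033 |
| 12 v 2 | 3.13 | 6.19 | 5.16 | 0.012 |
| 13 v 1 | 3.75 | 13.5 | 9.35 | 0.0016 |
| 13 v 0 | 4.06 | not finite | 28.1 | 0.0002 |

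The last pair is close to the rates in step 3 (320 × 0.04 = 12.8; 320 × 0.0025 = 0.8). Losing one control event moves the result across 0.05 in the first pair and not in the other two. The estimate moves in all of them: from 10 v 3 to 10 v 2 the adjusted odds ratio rises by 4.31/3.07 − 1 = 40%.

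**Step 5. How many controls could be affected.** The protocol says "Up to 1 in 20 people living with T2DM have liver cirrhosis". Taken at that ceiling, 320 × 0.05 = 16 controls. The true number should be lower, since known significant disease in active hospital follow-up and recent ELF or VCTE testing are exclusions. The share of these controls found outside primary care within 12 months is not in the document. If it were 3% to 10% (an assumption), and all of them entered surveillance, 0.5 to 1.6 events would be at issue. Zero is also possible.

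**The case against.** The strongest reply is that this is loose wording rather than an operative exclusion. The section headed Primary outcome names no referrer, the abstract would count a hospital-tested control, and no sentence says that a hospital-found case is a non-event. The letter sentence says where to look and who received the letter, not who wrote it. Taken strictly, the primary-care phrase would cast doubt on screening-arm events too, which suggests it was not meant as a strict filter. One could also argue that standard care here means risk-factor testing under the NICE guideline, so that counting only that pathway's yield is a legitimate choice of estimand.

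Much of this stands, and it rules out some stronger readings. A reader might infer that usual care will be undercounted as a matter of fact; the protocol does not establish that. A reader might infer that only the control proportion falls; the pathway drop-out allowed for in both arms means that a screened participant could be lost the same way. A reader might hold that hospital detection is the main way late disease presents; the protocol does not say so. A reader might infer that the cost-effectiveness model is distorted as well; its surveillance state is described for both cohorts with no condition on where the referral came from, so that is not shown. Nor does one lost event generally reverse the conclusion, as the 12 v 3 and 13 v 1 examples show.

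What the reply does not remove is the conflict itself. If only the guideline pathway's yield is wanted, the abstract and the Primary outcome section do not say so. If any route counts, the data-collection wording is wrong.

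**Conclusion.** The point holds as a conflict in stated text. The primary outcome has three different qualifying conditions, and the dated letter check is described for one arm only. The same control can be an event under the abstract and a non-event under a literal reading of the data-collection section.

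The likely direction of any bias is towards screening, resting on the assumption that most screened participants with advanced disease are found at the hub. Its size cannot be estimated from the protocol: neither the expected control events nor the share of usual-care diagnoses made outside primary care is given in the text, and the number affected may be zero. With few events expected, one or two reclassified controls could move the odds ratio materially and, at some plausible counts but not others, move the p-value across 0.05. It should be corrected before outcome extraction is finished.

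**What to change.** Use one definition in the abstract, the Primary outcome section and the data-collection section: first referral to, or contact with, secondary care or a community liver service for suspected liver disease, by any route, dated within 12 months of randomisation, and followed by referral to HCC surveillance.

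Apply it with the same record sources and the same evidence in both arms. Acceptable evidence would be any referral letter, clinic letter, discharge summary or imaging report in the record. Drop the from-primary-care condition and the controls-only letter check.

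Record the route for every event (GP, hub, specialist to specialist, admission, incidental imaging) and report the count restricted to primary-care or hub routes as a sensitivity analysis. Readers who prefer the narrower estimand can then see it.

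The cost is one sentence in the outcome definition and one extra field on the extraction form, filled during the record review already planned. The control rate may rise slightly, which would make the stated power slightly less favourable.

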### Setting

The study will be conducted in 16–20 primary care practices and diabetes community care hubs in Wessex (including Hampshire, Wiltshire, the Isle of Wight and Dorset (UK)). The setting of the study is important as it includes a range of existing community liver pathways which means the intervention is compared with a diverse representation of standard care—which is a representative of diverse interpretations of the current NICE guidelines.^32^

Community hubs will be used for research data collection including VCTE and blood sampling. Primary care centres will be identified via the local Primary Care Network and the Primary Care NIHR clinical research network. The number of practices we are using is justified in the later dedicated sections of the form.

Recruitment will take place from January 2024 and will be complete by April 2025. Outcome data collection will be completed by June 2026, and the cost-effective analysis will be completed by the study end date of 1 September 2026.

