### Arm 2—standard care—NICE guidelines based T2DM + additional risk factor testing

Participants in the standard care arm will not be contacted for VCTE, and following baseline data collection will have no further contact with the research team during the follow-up period—outcomes will be collected remotely from the medical record (see below).

Standard care varies across the study area but is based on 2016 NICE guidance (NG49) (figure 1).^32^ In the 2016 NICE NAFLD guideline, the presence of T2DM does not trigger an assessment for liver disease in the absence of other specific risk factors.^32^ ‘Risk factors’ to enter standard care vary in the study areas but broadly include harmful alcohol consumption, an elevated ALT and a fatty liver on ultrasound examination. If risk factor thresholds are met, then the usual care pathway varies further, but in all areas involve VCTE with or without a biomarker for liver fibrosis (eg FIB-4 or ELF) (figure 1). The variation in standard care is very important as it increases the external validity of our study by being representative of the heterogeneity across the UK.

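### The protocol's own dates allow about 30 months of record review only for the first recruits and about 14 for the last, so some surveillance decisions will be cut off, possibly more often in usual care

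*Protocol article*

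**What the plan says.** The primary outcome has two steps. A participant must first be referred with suspected liver disease, and the wording then counts those referred "within 12 months of randomisation who are subsequently referred for HCC surveillance" (Primary outcome). The first step has a 12-month limit. The second has none beyond the date of record review.

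Under Primary outcome data collection, usual-care records are searched for "a referral letter to secondary care or a community liver assessment service that was sent within 12 months of randomisation". The same section gives the review horizon and its purpose: "The primary care record review will take place up to 30 months from randomisation to ensure enough time for definitive decisions regarding HCC surveillance".

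The Setting section fixes the calendar: "Recruitment will take place from January 2024 and will be complete by April 2025", and "Outcome data collection will be completed by June 2026, and the cost-effective analysis will be completed by the study end date of 1 September 2026".

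The arms enter the pathway differently. In Arm 1, "Participants in this arm will be referred by the research team directly for liver fibrosis assessment at a community hub". In Arm 2, "Participants in the standard care arm will not be contacted for VCTE, and following baseline data collection will have no further contact". No time from randomisation to the Arm 1 assessment is stated.

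Under Data analysis, everyone randomised is analysed by logistic regression on a binary outcome, with exact or penalised estimation because few events are expected.

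**The concern.** The long review horizon is there so that hepatology can finish its assessment, which by the article's own account may involve repeat elastography, further fibrosis tests or biopsy. If the calendar shortens the horizon for later recruits, some participants who would be referred for surveillance will still be undecided at the last search. Unless the loss-to-follow-up plan says otherwise, a binary outcome on all randomised participants counts them as non-events.

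Two things are at stake. First, true events are lost in both arms, which reduces yield and power in a trial that already expects few. Second, the loss may differ by arm. A usual-care referral can come at any time up to month 12, whereas the research team starts the Arm 1 pathway itself. If Arm 1 is assessed soon after randomisation, its participants have more decision time before the common closing date. The observed outcomes and pathway drop-out rates then enter the decision model, where an undecided case could be read as drop-out.

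**Working it through.** **Reproducing the 30 months.** 1 January 2024 to 30 June 2026 is 29.9 months (29 counting month to month). The figure is therefore right as a ceiling for the first recruits.

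**Last recruits.** April 2025 to June 2026 = 14 months. After a month-12 referral, 14 − 12 = 2 months remain (1.0 to 2.9 by day). If Arm 1 referral occurs at month 1, 2 or 3 (assumed), 13, 12 or 11 months remain; at month 6, 8 months. A full 30 months for an April 2025 recruit would run to October 2027, about 13 months beyond the study end of 1 September 2026.

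**How common is the tight case?** Assume review time F uniform on 14 to 30 months and usual-care referral uniform on 0 to 12. Time left is 2 + u + v, with u uniform on 0 to 16 and v uniform on 0 to 12 (area 16 × 12 = 192).
- Under 3 months: u + v < 1, so 0.5/192 = 0.3%.
- Under 6 months: u + v < 4, so 8/192 = 4%.
- At least 12 months: 1 − 50/192 = 74% (72% if accrual is taken as 15 months, F from 14 to 29).
- Median: 2 + 14 = 16 months.

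**Effect on the comparison.** Add an assumed exponential lag from referral to decision, rate λ = ln 2 / median. With referral month R independent of F, the share of true events captured is

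1 − E[exp(−λF)] × E[exp(λR)].

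For a 6-month median, λ = 0.1155:
- E[exp(−λF)] = (0.1984 − 0.0313)/(16 × 0.1155) = 0.0904.
- Usual care, R on 0 to 12: (4 − 1)/(12 × 0.1155) = 2.164; captured 1 − 0.196 = 80%.
- Arm 1, R on 1 to 3: (1.4142 − 1.1225)/(2 × 0.1155) = 1.263; captured 1 − 0.114 = 89%. Ratio inflation 0.886/0.804 = 1.10.
- Arm 1, R on 3 to 9: (2.8284 − 1.4142)/(6 × 0.1155) = 2.040; captured 1 − 0.185 = 82%. Ratio inflation 1.01.

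The same formula gives:

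| Median lag | Usual care captured | Arm 1 captured (referral 1–3 mo) | Ratio inflation, 1–3 mo | 2–6 mo | 3–9 mo |
|---|---|---|---|---|---|
| 3 months | 94% | 98% | 1.04 | 1.03 | 1.01 |
| 6 months | 80% | 89% | 1.10 | 1.06 | 1.01 |
| 12 months | 58% | 67% | 1.16 | 1.09 | 1.01 |

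**Absolute difference.** Truncation shrinks the risk difference when the true ratio exceeds (1 − usual-care capture)/(1 − Arm 1 capture). With Arm 1 referral at 1 to 3 months this threshold is about 3.4, 1.7 (0.196/0.114) and 1.3 for median lags of 3, 6 and 12 months.

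**The case against.** Several points on the other side stand.

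- The 30 months is worded as a maximum, so the two sections do not contradict each other literally. What fails is the stated purpose for late recruits.
- A reader might infer that late usual-care referrals get 2 months while screened participants get a year. That sets the worst usual-care case beside a favourable Arm 1 case. Earlier usual-care referrals have longer, and a screened participant referred late would be squeezed equally.
- A reader might also infer that most participants lack enough time because, under uniform accrual, about 63% to 67% have under 24 months of review. The documents set no 24-month requirement, and on the same assumptions 72% to 74% of usual-care referrals have 12 months or more after the letter.
- A definite bias in favour of screening is not established. It depends on Arm 1 timing, which the article does not state, and almost vanishes if assessment is spread over months 3 to 9. Even where the ratio is inflated, the absolute yield may be understated, which works against screening. The inflation is also small beside sampling error with few events.
- Giving every participant 12 months from a month-12 letter would put the last search in April 2027, seven months after the study end. Replacing the primary regression would be a real change of analysis, not a trivial one.
- The loss-to-follow-up plan is in a supplement that is not shown and may already deal with pending decisions.

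These points limit the size and urgency of the concern. They do not remove the mismatch between the review horizon and the calendar.

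**Conclusion.** The point holds in a limited form and should be fixed, though it does not invalidate the design. The 14-month and 2-month figures follow directly from the stated dates. Some loss of events in both arms follows if any decisions are pending at the last search and are scored as non-events. A larger loss in usual care follows only if Arm 1 is referred early.

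The size rests on assumptions the documents cannot confirm: uniform accrual, usual-care referral uniform over 0 to 12 months, and exponential lags with medians of 3 to 12 months. Under these, ratio inflation is about 1.04 to 1.16 with Arm 1 referral at 1 to 3 months, falling to about 1.01 at 3 to 9 months. The direction of error in the absolute difference depends on the true effect.

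**What to change.** Reconcile the Setting and Primary outcome data collection sections, keeping the planned penalised logistic regression as primary:

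1. State that available review time runs from about 14 to 30 months according to recruitment date.
2. In both arms, record the date of the referral letter, and flag any surveillance decision still pending at the final search.
3. Run the final remote search for late recruits as late as the calendar allows.
4. Prespecify a sensitivity analysis that applies the same decision window from the referral letter in both arms and censors at record review. Censoring is needed because the longest window every participant could complete is 14 − 12 = 2 months.
5. Carry the censored estimate into the Markov model as a scenario.

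The cost is a little extra data extraction and analysis, and a less favourable description of follow-up. Review is remote, so no participant contact is added and the study end date need not move.
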